### Participant outcomes data collection

Participant outcomes data in a prospective full trial will be collected via two routes: questionnaires completed by the participants and routine maternity service data collected from the Trust. The task in the pilot, as explained, is to assess the completion rates and also to determine the optimum processes for collecting useable outcomes data.

#### Outcomes questionnaires general overview

The questionnaires will be administered as online and hard copies, with participants able to select their preferred mode. The research team will use a database to track the sending out and return of hard copies. To facilitate online surveys, an electronic participant-recorded outcome tool, provided by the PCTU, will be used. This will have the facility to email participants a link to questionnaires. All women will be offered a £10 voucher for each of the three questionnaires they complete. These will be handed to women who complete their questionnaire in the presence of a researcher and posted to women who submit their questionnaire without a researcher being present.

The questionnaires will be identified only with study ID number. The hard copies of the questionnaires will be stored in a locked filing cabinet in a pin code accessible office for the duration of the study. Data will be entered onto a database developed and maintained by the PCTU. For hard copy questionnaires, research team staff will do full double data entry for the primary outcome and double data entry on a 10% sample for other outcomes. Depending on identified error rates, the proportion of data double entered may be increased.

The participants’ questionnaires will be completed at three time points: baseline (8–12 weeks pregnant), first follow-up questionnaire (35 weeks pregnant) and second follow-up questionnaire (approximately 4 months after the baby is born). The baseline questionnaire will include demographic questions, a limited number of outcome measures and some questions relating to service preferences. The follow-up questionnaires will include outcome measures and some process questions relating to randomisation, attendance at antenatal care and preferences for providing outcomes information, see Table 2 for details on the questionnaires.

#### Baseline questionnaire

The baseline questionnaire will be provided by the researcher, as a hard copy or electronically on a tablet computer, for immediate completion following recruitment in the antenatal clinic. Completion will be prior to trial arm allocation being revealed to the women in order that knowledge of the type of care they will receive does not influence their responses. Women who cannot complete immediately, or want time to consider participation in the trial, will be given a hard copy (and an addressed/postage paid envelope) to post back or they can be provided with a link to the online survey to complete at home. These women will be informed of their trial arm status once the questionnaire has been received. If questionnaires that are taken away are not returned after 2 weeks, a telephone call will be made to offer completion over the phone with a researcher. For those women who do not speak English or who have limited literacy, the researchers will offer to make home/community visits to administer the questionnaires accompanied by a bilingual health advocate where required.

Feedback from our patient and public involvement (PPI) representatives on the draft baseline questionnaire suggested that this should be as short and simple as possible to be acceptable to the diverse community in the study. The validated measures within the questionnaire were perceived as particularly challenging and off-putting to potential participants. Two versions of the questionnaire will therefore be used to test acceptability—one, a shortened version of the other. A randomly allocated schedule of distribution of the two versions will be developed by an independent statistician. Approximately half the recruited women will be given the longer version and half the shorter, via sealed and numbered envelopes. Recruiters will be unaware of the allocation. Acceptability to participants of the different versions will be assessed by relative completion rates. The statistical implications of not having certain data at baseline will also be reviewed.

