### Sample size

The study will aim to recruit 24 participants from each of the three maternity units within the participating NHS Trust making a combined total of 72 women. Half of the recruited women in each area (up to 12 women) will be randomised to take part in the ‘Pregnancy Circles’ and half to receive standard antenatal care. This sample will not be powered to show differences between the trial arms on outcomes. Rather, the sample size has been determined to allow us to test the assumptions used in the sample size calculations for a full trial. This sample size will allow recruitment to take place in the three geographical areas in the NHS Trust where the Pregnancy Circles will take place, to allow us to test recruitment rates and to assess whether this differs by area. It will also allow us to explore uptake and retention rates to see whether our assumptions about the loss to follow-up are appropriate.

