If a woman is unsure about whether she wishes to participate in the trial, she will be able to contact the researcher after the booking visit. She will be given a copy of the consent form and baseline questionnaire to take away to be completed at home if she decides to participate. Stamped addressed envelopes will also be provided. She will be asked if she is happy to give her telephone number/email address to the researcher so that a reminder contact can be made to clarify whether she is interested in participating. If a woman does not wish to give this contact information, she will have the option to telephone the research team using the number given on the PIL.

Women who choose to participate in the ‘Pregnancy Circles’ will be asked to sign a consent form and to fill in a self-completed baseline questionnaire. Language support, as described below, will be offered for the completion of both, if required. It will be explained in writing and verbally that they can withdraw at any time if they so wish.

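### The long/short baseline questionnaire test is described among recruited women, so an undecided woman put off by her version can drop out of the denominator and deterrence is likely to be understated

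*Protocol article*

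**What the plan says.** The Baseline questionnaire section of the protocol article gives the reason for the test: patient and public representatives found the validated measures hard going and likely to discourage potential participants. Two versions are therefore distributed on a random schedule: "Approximately half the recruited women will be given the longer version and half the shorter, via sealed and numbered envelopes". The measure follows: "Acceptability to participants of the different versions will be assessed by relative completion rates".

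The default route is completion in clinic straight after recruitment. Women who cannot complete it then, or who want time to think about joining, take a hard copy or use an online link. On undecided women, Recruitment of participants says: "She will be given a copy of the consent form and baseline questionnaire to take away".

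Several features encourage return of either version:
- On timing: "Completion will be prior to trial arm allocation being revealed to the women". For those who take it away: "These women will be informed of their trial arm status once the questionnaire has been received".
- A telephone call after 2 weeks offers completion by phone, and home or community visits are offered to women with language or literacy needs.
- A £10 voucher is offered for each completed questionnaire (Outcomes questionnaires general overview).

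The clinic proforma under Pilot trial feasibility outcomes counts women eligible, approached, declining and consenting. It does not mention questionnaire version.

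**The concern.** The question concerns potential participants, but the population named is recruited women. The two differ where the questionnaire reaches a woman before she has consented. If the long version helps her decide not to join, she returns neither document. Hers is the reaction the test was set up to find, and it is missing from both numerator and denominator. This is selection after randomisation, by an event that the randomised version may cause.

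The result will inform the choice of baseline instrument for the full trial. Consent to randomisation is also a progression criterion (Table 1). A long version that costs some recruitment could look nearly as acceptable as the short one.

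**Working it through.** **Numbers available.** Sample size states: "The study will aim to recruit 24 participants from each of the three maternity units". 24 × 3 = 72, which reproduces the stated total, and 72 / 2 = 36 recruited women per version. No power, margin or expected completion rate is given for this comparison.

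**Who stays in the denominator.**
- Consents in clinic, is given a version, does not return it: recruited, and counted as a non-completer. The measure works.
- Undecided, takes both documents home, returns neither: not recruited, and not counted.
- Undecided, returns both: recruited, and counted as a completer.

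**Effect of the second case.** Let r be the share of women handed a version who return it, and f the share of non-returners who still count as recruited, taken as equal for both versions. The observed completion rate is r / (r + (1 − r)f). Assume r = 0.80 (short) and 0.60 (long). Neither value is in the document.

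| f | Short | Long | Gap (points) | Rate ratio | Fisher power, 36 v 36 |
|---|---|---|---|---|---|
| 1 | 80.0% | 60.0% | 20.0 | 1.33 | 0.37 |
| 0.50 | 88.9% | 75.0% | 13.9 | 1.19 | 0.24 |
| 0.25 | 94.1% | 85.7% | 8.4 | 1.10 | 0.10 |
| 0.10 | 97.6% | 93.8% | 3.8 | 1.04 | 0.01 |
| 0 | 100% | 100% | 0 | 1.00 | 0 |

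For example, at f = 0.25: 0.80 / (0.80 + 0.20 × 0.25) = 0.80 / 0.85 = 94.1%, and 0.60 / (0.60 + 0.40 × 0.25) = 0.60 / 0.70 = 85.7%. Power uses a two-sided 5% Fisher test, also an assumption. The row f = 1 describes women who consent in clinic. The row f = 0 describes undecided women if every non-returner keeps both documents. The whole sample lies between, at a point the document does not fix.

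**How general the shrinkage is.** Since 1 / observed rate = 1 + f(1/r − 1), the ratio of completion rates always moves towards 1 as f falls. The gap in points has slope f / (r + (1 − r)f)² in r. That slope is below 1 when r > √f / (1 + √f), a bound that never exceeds one half, so the gap shrinks whenever both return rates exceed 50%. An odds ratio would be unaffected by a common f above zero, but the plan compares completion rates.

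**Precision near the ceiling.** At 36/36 in both versions the Wilson lower limit is 36 / (36 + 3.84) = 0.904, so the 95% Newcombe interval for the difference is −9.6 to +9.6 points. With one version at 36/36, the other must fall to 30/36 for Fisher p < 0.05 (p = 0.025; 31/36 gives 0.054). Power is 0.15 for 95% v 85% and 0.08 for 98% v 90%.

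**The case against.** A reader might infer that, because return is required before a woman learns her arm, both versions must sit near 100% and the test cannot show a difference whatever the truth. The document does not support that:
- It states no expected completion rate.
- The condition is on being told the arm. Nothing says an unreturned questionnaire removes a consented woman from the recruited count.
- The default route hands over the questionnaire after recruitment, and the two-week call shows that non-return is foreseen.
- Receipt does not require every item to be answered, so item completeness could differ by version even with full return.

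Other points have force. The sentence on completion rates names no denominator; recruited women appear in the sentence on distribution, so counting by issue is compatible with the text. The mechanism reaches only undecided women, whose number is unknown. Numbered envelopes and a database tracking hard copies sent and returned already supply much of a log. Reasons for declining, interviews and the question on trial procedures in the second follow-up questionnaire will also bear on acceptability, though none is said to be broken down by version. Nor does counting by issue cure imprecision: with assumed counts of 36/45 v 36/40, the 10-point gap has a Wald 95% interval of about −5 to +25.

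These points limit the concern without removing it. Recruited women are the only population the section names, versions go to women outside it, and an analysis plan written later cannot rebuild a denominator of women issued each version if version was not logged at issue.

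**Conclusion.** The concern holds for undecided women. For them, completion among recruited women depends on a decision the version can affect, so the measure is likely to understate deterrence. For women who consent in clinic it remains valid, but the voucher, researcher support, two-week call and withheld allocation push both versions up and reduce contrast. The size cannot be stated: it depends on the share of undecided women and on return rates, neither of which is given. The table shows the range under assumed returns of 80% and 60% and a common f. Whatever the denominator, about 36 recruited women per version supports description only.

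**What to change.** Record the version at the moment of issue for every woman, on paper, tablet or online link, by extending the numbered envelopes and the planned hard-copy tracking. Then state in the Baseline questionnaire section that:
- the denominator is every woman issued a version, with non-return counted as non-completion;
- women who had consented and women still undecided at issue are shown separately;
- returns before the two-week call, and missing items on the questions common to both versions, are also reported by version;
- the comparison is descriptive, with intervals.

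The cost is one extra field in a log and a few lines of text. The drawback is that women undecided about the trial itself add noise to both versions, which is why the two groups should be shown separately.

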#### Follow-up outcomes questionnaires

For the intervention group, the first follow-up questionnaire will be provided at the completion of the Pregnancy Circle session when women are 35 weeks pregnant. A researcher will provide a hard copy or online version (on a computer tablet) depending on a woman’s preference. Interpreters will be at the group, where appropriate, and will assist with completion. Anyone who would prefer to complete the questionnaire at home, for whatever reason, will be supported to do so. For the control group, the questionnaire for the first follow-up will be completed, with the support of a researcher, in the antenatal clinic at a woman’s 35-week routine appointment. Where this is not possible for any individual woman, the questionnaire will be sent out for completion at home.

For women in both arms of the trial, the second follow-up questionnaire will be completed at approximately 4 months postnatal. Depending on earlier specified preferences, women will be sent hard copies to home addresses with a self-addressed envelope (SAE), and/or women will be emailed a link to an online version.

The research team will check with antenatal clinic staff, prior to contacting women about follow-up questionnaires, to ensure that there are no reasons (for example the loss of a pregnancy) why a woman should not be approached. The same pattern of reminders for non-response to the follow-up questionnaires will be followed as used for the baseline questionnaire (see above). Similarly, visits will be offered with a bilingual health advocate where there are language requirements. Any woman who requests withdrawal from the intervention following allocation will be asked if she is prepared to continue to provide data for the study. If she is, she will be given outcomes questionnaires as above.

#### Routine maternity services data

As Table 2 indicates, some participant outcomes data (including the primary outcome data) will be assessed through patient records, rather than from self-completed questionnaires. Specific permission for use of patient records is part of the study consent form. The pilot trial will use two routes to access these data: (1) through electronic medical records and (2) through an audit of paper maternity notes. The research team will check reliability and data quality of the two versions of medical records and will thus determine the best route for accessing the required outcomes data in a full trial. The team’s previous work undertaken via a Programme Development Grant suggested that some outcomes data on attendance for antenatal care was complete in maternity notes but incomplete in the electronic record [34].

For the data extraction from electronic patient records, the research team will develop a proforma for the Trust Informatics team (the team responsible for managing electronic data). We will supply them with a list of participants’ hospital numbers and study IDs, so no names will be required. A standard operating procedure (SOP) will be generated, in conjunction with the data management team at the PCTU, for the secure transfer of data from the Trust Informatics departments to the PCTU.

For the paper maternity notes, a research team member who is blinded to the allocation to study group will conduct an audit by extracting data manually from the participants’ paper records within the hospital setting. A proforma will be used that will anonymise the information collected, using study ID numbers. The data will be entered onto an electronic database and securely transferred to the PCTU using the SOP developed by the PCTU data management team.

#### Method of analysis

Participant outcomes data will be analysed for completeness and for usability in a full trial. Outcomes will be summarised in each arm using mean and standard deviation for continuous data, number and percentages for categorical data.

#### Data handling

The PCTU data managers will co-ordinate the management process for the outcomes data. Electronic systems will be put in place that automatically manages the process of sending out vouchers and reminders for questionnaires. It will also involve supporting the integration of the outcomes data from participant questionnaires, electronic maternity records and maternity audit data. A data management plan will document the processes required to enable integration of the datasets in a manner that maintains standardisation of data and blinding of the statisticians. All databases and analysis files will be stored on a secure server and accessed via a secure network. Access is restricted to authorised personnel only and via secure, password-controlled, role-based access.

### Economic evaluation

In the full trial, we plan to calculate the cost-effectiveness of Pregnancy Circles compared to control from conception until 4 months postpartum. NICE recommend that cost-effectiveness is calculated as the cost per quality-adjusted life year (QALY) gained [35]. This methodology presents significant challenges for this study. Group antenatal care has potential health implications and costs for both the mother and infant, in particular as a key aim of group antenatal care is better engagement of women with maternity and other health care services. This could potentially increase some service costs in the short term, but also improve the health and well-being of the infant and mother in the immediate period, and also in the medium and longer terms. Increasing the proportion of infants vaccinated is the most straightforward example of improved engagement with health care services. Although measuring QALYs for the mother is possible, when and how to start measuring QALYs from the perspective of the infant is controversial and methodologically challenging.

In the pilot trial, the economic evaluation will explore alternative utility measures via the participant questionnaires. Additionally, we will involve women in defining what a ‘healthy birth’ is, so that we will be able to calculate the incremental cost per additional healthy birth for group antenatal care compared to control, using this composite measure. In the early months of the pilot, we will work in consultation with our lay co-investigators and with the local Maternity Services Liaison Committees, to determine whether the suggested questions to be used in the follow-up questionnaires to capture women’s satisfaction with antenatal care are sufficient, or whether additional ones need to be included. Responses to antenatal care satisfaction questions plus relevant outcomes data will be included in the composite. Initially, we will conceptualise a ‘healthy birth’ as occurring if women:Were largely satisfied with their care during pregnancyFelt involved in decision-making about their careHad low antenatal distressDid not suffer postnatal depression (within the follow-up period)Perceived that they had good levels of information and professional support (during pregnancy, labour and delivery)Had a baby with gestational age at delivery, ≥ 37 weeks.Did not have a caesareanHad a baby with a birthweight > 2500 gFelt their care was responsive to cultural, religious/spiritual and linguistic needs (i.e. individualised, culturally sensitive care).

We will use the data collected during the pilot to assess the validity of this composite measure and to develop algorithms for how births might be classified on a continuum from ‘healthy’ to ‘unhealthy’.

Our assumption for the full trial is that costs will include the cost per pregnant woman of group antenatal care as well as mother and infant primary and secondary care costs from conception until 4 months postpartum. As such, in this pilot trial, use of primary and secondary care will be collected via additional questions on the participants’ baseline and follow-up questionnaires. Unit costs will be obtained from published national sources. Confidence intervals and cost-effectiveness acceptability curves will be calculated using bootstrapping (sampling with replacement). The perspective we will adopt for the economic evaluation will be health and social care costs. We will validate our resource use data as part of the pilot study by checking resource use reported by women in a sample of questionnaires against medical records. For the sensitivity analysis, we will use non-parametric bootstrap to construct confidence intervals for trial data: one-, two- and multi-way deterministic analyses for any assumptions made; if a decision model is constructed, we will do a full probabilistic sensitivity analysis. Trial missing and censored data will be handled the same way in the economic evaluation as for the statistical analysis.

### Monitoring and auditing

The pilot trial will be overseen by a steering committee. This group will meet at least once face-to-face during the 15 months of the pilot trial and then continue to meet yearly if the main trial goes ahead. This committee will be responsible for overseeing the pilot and the main trial, ensuring scientific quality and clinical relevance, and adherence to ethics and research governance. All key collaborators on the pilot trial will attend this committee, as well as a range of experts who are not directly involved in the pilot, including a chair with relevant expertise, a statistician, an economist and a PPI member.

The PCTU quality assurance (QA) manager will conduct a study risk assessment in collaboration with the CI. Based on the risk assessment, an appropriate study monitoring and auditing plan will be produced according to PCTU SOPs. This monitoring plan will be authorised by the sponsor before implementation. The PCTU QA manager and the sponsor will agree on any changes to the monitoring plan. The CI will ensure that safety monitoring and reporting is conducted in accordance with the sponsor’s requirements. This will include appropriate processes for management of adverse events.

